#### 3.3.2. Clinical Measurements

Blood pressure and heart rate are measured using a calibrated Omron automatic blood pressure monitor. Height is measured to the nearest 0.5 cm using a calibrated wall-mounted stadiometer. Weight is measured to the nearest 0.1 Kg using a calibrated portable digital scale. BMI is calculated as kg/m^2^ for women and as BMI z-score for offspring [23]. Waist circumference is measured to the nearest 0.1 cm by applying the tape directly on the skin, horizontally at the lateral level midway between the iliac crest and the lowest lateral portion of the rib cage. Hip circumference is measured to the nearest 0.1 cm over the widest part of the gluteal region. Offspring are weighed without shoes and lightly dressed. Body fat is measured by bioelectrical impedance analysis (Bodystat 1500, Bodystat Limited, Douglas, Isle of Man, Great Britain). Skinfolds are measured at three different sites (triceps, subscapular, suprailiac, measured twice at each site with calibrated calipers (Harpenden, Baty International, West Sussex, Great Britain) to the nearest 0.1 mm (if results differed by >1.0 mm, they were measured a third time)) [18]. Means of the two skinfold measurements, or the two closest measurements if three measurements were made, are used for analysis. All participating centers received specific training for the skinfold measurements in order perform these measurements correctly. In addition, instructional videos were made for skinfold measurements to refresh training if necessary.

All anthropometric measurements are taken twice, and if the differences exceed 0.5 cm or 0.5 kg for the anthropometric measurements, or 5 mmHg for blood pressure measurements, a third measurement is taken. In all analyses, the mean value of the measurements is used. The anthropometric measurements are performed by a trained nurse, physician or clinical trial assistant.

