### 3.4. Outcomes of the Study

#### 3.4.1. Primary outcome

For mothers: A disorder of glucose metabolism: T2D defined by the 75 g OGTT and/or HbA1c, or prediabetes defined as IFG and/or IGT by the American Diabetes Association (ADA) criteria [1].

For offspring: BMI z-score as a continuous variable [23].

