#### 3.6.2. Statistical Analyses

Differences between groups will be analyzed using linear models in the case of continuous outcomes and logistic regression models in the case of binary outcomes. Results will be presented as mean differences or odds ratios, respectively, with 95% confidence intervals.

Analyses will be performed separately and analogously for comparing (1) GDM versus non-GDM, and (2) the three gestational glucose tolerance groups. In the analyses on offspring, interaction effects between the group and the gender of the offspring will be analyzed. Such an interaction effect would mean that the differences in outcome between the groups is different for males and females. In the case of a group by gender interaction effect, results will be presented by gender. In the absence of such an interaction, the main effects for the group will be presented.

Multivariable models will be used to correct for possible confounders. Correction for confounders will be performed in a stepwise fashion. For maternal outcomes, covariate adjustment will be performed for time since pregnancy in a first step. Maternal variables during pregnancy will be added as confounders in a second step, and maternal variables during follow-up will be further added in a third step. For outcomes in offspring, covariate adjustment will be performed for the child’s age and center in a first step. Maternal variables during pregnancy will be added as confounders in a second step, and offspring variables during follow-up will be further added in a third step.

Maternal characteristics during pregnancy include variables such as age, pre-pregnancy BMI, blood pressure, and smoking. Follow-up characteristics include variables such as mothers’ age, BMI measured during the OGTT and smoking for maternal outcomes, and variables such as children’s age and BMI at the time of the clinical examination for analyses on offspring outcomes. The confounders included in each analysis will depend on the concrete outcome that is being analyzed. Correction is indicated if the confounder is known or suspected to be associated with the predictor of interest (group) as well as the outcome. Confounders will be determined a priori based on expertise and literature. If the number of indicated confounders is too large in relation to the sample size, further selection will be based on univariable analyses on the association between the confounder and the group.

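### Adjustment step 3 treats variables measured years after the exposure as confounders, so its group estimate is not a confounding-corrected effect

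*Protocol article*

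**What the plan says.** All from the protocol article.

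- **Purpose of adjustment** (3.6.2): "Multivariable models will be used to correct for possible confounders". This sentence introduces all three steps.
- **The steps** (3.6.2): step 1 is time since pregnancy for mothers, and child's age and center for offspring. Step 2 adds maternal variables from the pregnancy. For maternal outcomes, "maternal variables during follow-up will be further added in a third step"; for offspring outcomes, "offspring variables during follow-up will be further added in a third step".
- **Examples for step 3** (3.6.2): for mothers, age, current BMI and smoking; for children, age and "BMI at the time of the clinical examination for analyses on offspring outcomes". Both lists are given as examples, and the text says the choice depends on the outcome analysed and is made a priori from expertise and literature.
- **Criterion** (3.6.2): "Correction is indicated if the confounder is known or suspected to be associated with the predictor of interest (group) as well as the outcome". If too many variables qualify, the choice narrows by univariable association with group.
- **Primary outcomes** (3.4.1): for offspring, "BMI z-score as a continuous variable"; for mothers, type 2 diabetes, "or prediabetes defined as IFG and/or IGT by the American Diabetes Association (ADA) criteria".
- **How child BMI is expressed** (3.3.2): "BMI is calculated as kg/m^2^ for women and as BMI z-score for offspring".
- **Timing** (3.3): one visit, three to seven years postpartum.
- **Hypothesis** (section 1, last paragraph): each degree of gestational glucose intolerance predicts distinct later courses of weight, beta-cell function, insulin sensitivity and glycaemia, in women and in offspring.

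**The concern.** A confounder is a cause, or a marker of a cause, of both exposure and outcome. A BMI or smoking status recorded years after the index pregnancy cannot have caused the glucose group in that pregnancy. On the plan's own hypothesis, later weight may be a consequence of the group. The written criterion does not separate the two cases, because a variable on the pathway from group to outcome is associated with both. The fallback selection by association with group does not separate them either, and tends to keep variables that the group affects strongly.

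What is at stake is the interpretation. If the group effect changes between steps 2 and 3, the text as written invites the reading that step 2 was still confounded and step 3 corrects it. The change may instead reflect removal of a real pathway, or bias introduced by conditioning on a consequence of the group. The offspring primary outcome needs particular care, because the named covariate and the outcome are built from the same height and weight at the same visit.

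**Working it through.** **1. The plan's own figures.** Power for two proportions with pooled variance, two-sided 5%, n = 125 per group: power = Φ[(d − 1.96·SE0)/SE1], with SE0 = √(2·p̄(1−p̄)/n) and SE1 = √([p1(1−p1)+p2(1−p2)]/n).

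- 12% vs 26%: d = 0.14, SE0 = 0.0496, SE1 = 0.0488, so Φ(0.875) = 80.9% (stated 81%).
- 4% vs 26%: d = 0.22, SE0 = 0.0452, SE1 = 0.0430, so Φ(3.06) = 99.9% (stated 99%).

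Both reproduce. They concern an unadjusted chi-square test, so nothing below changes them.

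**2. What step 3 estimates for mothers.** The documents give no path coefficients, so these are assumed. Pre-pregnancy BMI is standard normal, plus 0.4 in the exposed group. Follow-up BMI = pre-pregnancy BMI + a·group + noise (SD 0.5). Log-odds of the outcome = −2.3 + 0.9·group + 0.6·follow-up BMI. The direct odds ratio is exp(0.9) = 2.46. Step 2, which omits follow-up BMI, should give about exp(0.9 + 0.6a). Simulation with 400,000 women:

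| Effect of group on later BMI (a) | exp(0.9 + 0.6a) | Step 2 OR | Step 3 OR |
|---|---|---|---|
| 0 | 2.46 | 2.42 | 2.45 |
| 0.2 | 2.77 | 2.72 | 2.44 |
| 0.5 | 3.32 | 3.32 | 2.49 |
| −0.3 | 2.05 | 2.02 | 2.45 |

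There is no confounding left after step 2 in any row, yet step 3 differs clearly from step 2 whenever a is not zero. The direction depends on whether the group raises later BMI or lowers it, for example through lifestyle change after a diagnosis.

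**3. Collider bias.** Add an unmeasured common cause of follow-up BMI and the outcome, with coefficient 0.5 on each. The odds ratio then goes from 2.96 to 1.91 (a = 0.5) and from 1.91 to 2.79 (a = −0.3). Step 3 now misses even the direct value of 2.46, on either side. Part of the shortfall at 1.91 may be non-collapsibility of the odds ratio; that cannot explain 2.79.

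**4. Offspring BMI z-score, if the child's BMI were entered.** If BMI is expressed as the z-score (3.3.2), covariate and outcome are the same variable and the group coefficient is zero. If it is entered in kg/m², take an assumed growth-curve transform (median about 15.3, coefficient of variation about 8.5%, skewness parameter −1), ages 3 to 7, 125 per group, 300 replicates, and a linear model on group and age:

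| True difference (SD) | Without child's BMI | With child's BMI | Lost |
|---|---|---|---|
| 0.20 | 0.203 | 0.003 | 98% |
| 0.30 | 0.309 | 0.006 | 98% |
| 0.50 | 0.506 | 0.010 | 98% |

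R² with BMI in the model is about 0.98. The loss is built into the model and says nothing about biology.

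**5. Age terms.** Mother's age at follow-up equals her age in pregnancy plus time since pregnancy, so a model with all three has one redundant column. Dropping any one of them leaves the group coefficient unchanged. Repeating the child's age in steps 1 and 3 is equally harmless.

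**The case against.** The best defence is that the article does not commit to the worst model. The step 3 variables are examples that serve many outcomes together, the covariates are said to depend on the outcome, and they are to be chosen beforehand from expertise and literature. A competent analyst would not adjust BMI z-score for BMI. This stands: a reader might infer that the offspring primary analysis will be adjusted for the child's own BMI, but the text does not say so. What is missing is an exclusion, and the 98% figure applies only if that model is run.

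Second, steps 1 and 2 list no follow-up BMI or smoking, so estimates free of later weight are already planned, and nothing declares step 3 to be the answer. This also stands. Naming a main step could normally be left to an analysis plan that is not shown.

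Third, whether an association persists given current BMI is a fair question. The Introduction cites studies that asked it, and current BMI also reflects shared genetics and family environment, so it is not purely a mediator. That supports keeping step 3. It does not support calling it confounder correction.

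A reader might also infer that step 3 always pulls the effect toward zero. The maternal scenarios show otherwise.

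What the defence does not answer is the criterion itself. It is stated, it applies to all three steps, and it admits consequences of the group.

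**Conclusion.** The concern holds as a fault in a stated rule and in how step 3 is labelled. Section 3.6.2 admits consequences of the gestational glucose group as confounders, while the Introduction expects group to influence later weight. The step 3 estimate is at best a direct effect, is open to collider bias, and can lie on either side of the step 2 estimate. A change between the two steps cannot be read as confounding removed.

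The size depends on assumptions that the documents do not supply. The maternal odds ratios rest on assumed path coefficients and show direction and order of magnitude only. For BMI z-score the loss is close to total, but only if the child's BMI is entered, which the outcome-specific wording leaves room to avoid. The redundant age terms bias nothing. Sample size and stated power are unaffected.

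**What to change.** Wording changes to section 3.6.2 or the analysis plan, with no change to data collection or sample size:

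1. Replace the criterion: a confounder is a suspected common cause of group and outcome that arises before or at the index pregnancy and is not affected by the group. Time since pregnancy, child's age and center stay as design terms in step 1.
2. Name step 2 as the main adjusted model, estimating the total effect of group.
3. Relabel step 3 as an exploratory analysis of the effect not explained by follow-up variables, and note that it is open to bias from unmeasured common causes of those variables and the outcome.
4. State that current BMI and weight are not covariates for BMI-defined outcomes: child BMI z-score and overweight/obesity, and maternal BMI and overweight/obesity.
5. Optionally, drop mother's follow-up age and the repeated child's age from step 3. This is tidying and does not alter the group estimate.

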### 3.7. Quality Control Procedures

Participating sites started recruitment after a first initiation visit. During the course of the study, the study monitor will perform periodic monitoring visits to ensure that the protocol is being followed. We plan at least a yearly monitoring visit for all sites. The coordinators of the study may review source documents to confirm that the data recorded on CRF pages are accurate. Collected data are recorded in the Good Clinical Practice (GCP) compliant Electronic Data Capture (EDC) platform ‘Research Data Capturing’ (REDCap). The monitor can assure data quality in the eCRF by sending queries to the local coordinators, in addition to on-site monitoring every four to six months. Our study has provided detailed standard operating procedures describing data collection during the study visit and blood sample collection.

## 4. Discussion

The BEDIP-FUS study will contribute to the push for more studies to determine the long-term metabolic risk of women across different gestational glucose tolerance groups based on the 2013 WHO criteria. Applying these 2013 WHO criteria for GDM could result in a greater percentage of women being diagnosed with mild forms of GDM, which might lead to a lower portion at risk for postpartum glucose intolerance. Studies are needed to determine the long-term metabolic risk of women across different gestational glucose tolerance groups based on the 2013 WHO criteria. Prospective studies are also needed to evaluate novel biomarkers, such as glycated CD59, to predict the long-term metabolic risk in woman and offspring. These results might help us to find a more accurate and patient-friendly way of screening for glucose intolerance, and may help to stratify women and offspring with a differential risk of developing an adverse cardiometabolic profile later in life.

To the best of our knowledge, we are the first study to investigate the impact of BMI, adiposity and different degrees of glucose intolerance on the metabolic profile and future risk for type 2 diabetes (T2D) in women and offspring across different gestational glucose tolerance groups in pregnancy based on the 2013 WHO criteria. In addition, we will also investigate whether different glucose tolerance groups measured with a 50 g GCT (cut-off: 130 mg/dL) followed by a 2 h 75 g OGTT identifies distinct trajectories of β-cell function, insulin sensitivity, and glycaemia approximately five years postpartum.

Studies provide no evidence yet that treating GDM in pregnancy can reduce the future risk for obesity and glucose intolerance in mothers and offspring. Reduction of macrosomia at birth was seen in women with GDM who received intensified glucose-lowering treatment, but follow-up studies of offspring showed no decline in childhood obesity or metabolic dysfunction in these children at the age of 4–10 years [42,43]. However, in an American study, sex-specific differences were seen, with a decreased frequency of impaired fasting glucose, lower fasting glucose, and lower insulin resistance in female offspring but not in male offspring [43]. Differing sensitivities to hyperglycemia in utero may result in long-term sex-specific programming. Additional studies are needed to understand the separate role and the combined potential superimposing effect of maternal hyperglycemia, maternal obesity during pregnancy and paternal BMI on the metabolic health of offspring. Moreover, data on the metabolic profile of offspring of women diagnosed with GDM according to the 2013 WHO criteria are scarce. Studies should also investigate sex differences in metabolic profiles in the offspring. With the BEDIP-N follow-up study we aim, therefore, to also evaluate potential sex differences in long-term metabolic risk across different gestational glucose tolerance groups in pregnancy.

A major strength of our study is that all women received both a GCT as well as an OGTT during pregnancy, allowing investigation of the impact of different glucose tolerance groups during pregnancy on the long-term glucometabolic risk of women and their offspring. We also have a large dataset on pregnancy and delivery outcomes for both mother and offspring. A limitation of our study is that our cohort mainly consists of Caucasian women.

## 5. Conclusions

Our study may help individualize the follow-up and intervention strategies in women and offspring with a history of GDM and different degrees of glucose intolerance based on the 2013 WHO criteria.

## Figures and Tables

**Figure 1 jcm-12-01025-f001:**
[figure not shown]
Study flowchart. BEDIP: Belgian Diabetes in Pregnancy; GDM: gestational diabetes mellitus; GCT: glucose challenge test; NGT: normal glucose tolerant (=normal OGTT); BEDIP-FUS: BEDIP follow-up; OGTT: oral glucose tolerance test; min: minutes; HbA1c: hemoglobin A1c; BMI: body mass index.

## Data Availability

This is the publication of the study protocol of an ongoing study. Data of the study are not available for publication, since recruitment is ongoing. Data sharing is not applicable to this article.
